### Sample size

The sample size is based on the ability to detect a difference on the primary outcome only and not on the inclusion of baseline measures as covariate. On the CORE-OM, 5.0 points is the accepted Reliable Change Index in service evaluations.^53 54^ In contrast, 2.5 points is held as the upper limit of what would be considered a change compatible with equivalence ([name], personal communication, 2015) in trials comparing two interventions. Other trials using the CORE-OM for mental health interventions versus treatment as usual or waiting list controls have achieved mean between group differences in change score of between 3.5 and 7.8.^55 56^ An SD of 5.6 was found in the pilot trial.^41^ However, larger clinical studies have reported larger SDs of approximately 7.5.^57^

Given the uncertainty, in both SD and the appropriate minimally clinically important difference (MCID) for the CORE-OM, we calculated sample sizes for different scenarios based on the range of values for these two parameters (see table 2). This is equivalent to aiming to be able to detect a minimum effect size of 0.26 (ie, small to medium).

**Table 2 T2:** Sample size (for each group) based on different values of SD and MCID for the Clinical Outcomes in Routine Evaluation-Outcome Measure

		SD		
		5.5	6.5	7.5
Change to be detected (MCID)	5.0	26	36	48
	4.5	32	44	59
	4.0	40	56	74
	3.5	52	73	97

At 90% power and two-sided alpha of 5%.

MCID, minimally clinically important difference.

Based on the conservative scenario of an MCID of at least 3.5 and a common SD of 7.5, we will require CORE-OM data on 97 participants in each group at 90% power and 5% alpha. Using an attrition rate of 30%, 140 participants are required per group. Follow-up rates of 63% and 55% were achieved in feasibility and pilot work.^41^ However, with learning from the pilot trial and assistance from the new Community Rehabilitation Companies (CRCs), which now supervise virtually all prison leavers for at least 1 year, an attrition rate of 30% or less is achievable.

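### The stated minimum effect size of 0.26 does not match the sample-size table: the chosen scenario (3.5 points, SD 7.5) is a standardised effect of 0.47

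*Protocol article*

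**What the plan says.** The Sample size section of the protocol article reports that both the SD and the minimally clinically important difference (MCID) of the CORE-OM are uncertain. Table 2 therefore gives numbers per group for differences of 3.5 to 5.0 points and SDs of 5.5 to 7.5. The text that introduces the table adds: "This is equivalent to aiming to be able to detect a minimum effect size of 0.26 (ie, small to medium".

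After the table the section picks one cell: "Based on the conservative scenario of an MCID of at least 3.5 and a common SD of 7.5". From that cell, "we will require CORE-OM data on 97 participants in each group at 90% power and 5% alpha". It then allows for loss to follow-up: "Using an attrition rate of 30%, 140 participants are required per group". The section also states that the calculation rests "not on the inclusion of baseline measures as covariate". No derivation of 0.26 is given, and the figure appears nowhere else in the article.

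**The concern.** For a two-group comparison of means, the standardised effect is the difference divided by the SD. The adopted cell has the smallest difference and the largest SD in Table 2, so it fixes the smallest standardised effect that the table covers. That value is well above 0.26, so the sentence and the table cannot both be right.

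The minimum detectable effect tells a reader how sensitive the trial was designed to be on its primary outcome. At 0.26 the article claims a markedly more sensitive design than 97 analysed participants per group can deliver.

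**Working it through.** **Inputs**, all from the Sample size section unless stated: 90% power; two-sided alpha 5%; 1:1 allocation (Design section); difference 3.5; SD 7.5; 97 analysed per group; 30% attrition; no covariate adjustment.

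**1. Reproduce the plan's own numbers.** With n per group = 2(1.960 + 1.282)² × (SD/difference)²:

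- 3.5 points, SD 7.5: 2 × 10.507 × (7.5/3.5)² = 96.5, rounded up to 97, as stated.
- The same formula reproduces the other eleven cells of Table 2 exactly.
- Attrition: 97/0.70 = 138.6, so 139; the article's 140 is this figure with slight rounding up.

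**2. Standardised effects in Table 2** (difference/SD):

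| Difference | SD 5.5 | SD 6.5 | SD 7.5 |
|---|---|---|---|
| 5.0 | 0.909 | 0.769 | 0.667 |
| 4.5 | 0.818 | 0.692 | 0.600 |
| 4.0 | 0.727 | 0.615 | 0.533 |
| 3.5 | 0.636 | 0.538 | 0.467 |

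The smallest is 0.467, in the adopted cell. Working back from n gives the same answer: (1.960 + 1.282) × √(2/97) = 0.465 (0.468 with the t distribution).

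**3. What 0.26 would mean.** At SD 7.5 it is 0.26 × 7.5 = 1.95 points. For 3.5 points it would need an SD of 3.5/0.26 = 13.5. Neither value is in the table.

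**4. Can another definition give 0.26?** None that was tried does.

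- 97 per group, two-sided: 0.402 at 80% power, 0.281 at 50% power.
- 97 per group, one-sided, 90% power: 0.420.
- All 140 per group analysed, 90% power: 0.387.
- Cohen's f = 0.467/2 = 0.233.
- As a correlation: 0.467/√(0.467² + 4) = 0.227.
- 2.5/7.5 = 0.333.

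**5. Power at 0.26, unadjusted.** With 97 per group, 0.26 × √(97/2) = 1.811. Power is Φ(1.811 − 1.960) = 44.1% (43.7% with the t distribution). With all 140 per group analysed it would be about 58%.

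**6. Size needed for 0.26.** 2 × 10.507/0.26² = 310.9, so 311 per group by the normal formula and 312 with the t distribution, against the planned 97.

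**7. Allowing for baseline adjustment.** The section on data management and statistical analysis plans to adjust the primary analysis for the baseline score. The article gives no correlation between baseline and 6-month scores, so the values below are assumptions. Adjustment multiplies the residual SD by √(1 − r²).

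| Assumed r | Detectable effect, 90% power, 97 per group | Power at 0.26 (t) |
|---|---|---|
| 0.3 | 0.44 | 47% |
| 0.5 | 0.40 | 55% |
| 0.7 | 0.33 | 71% |

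Reaching 0.26 at 90% power with 97 per group would need √(1 − (0.26/0.465)²), a correlation of about 0.83.

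**The case against.** The strongest reply is that nothing in the design depends on 0.26. Table 2, the 97 and 140 per group and the total of 280 all follow from 3.5 points and SD 7.5, which the section states openly, so a reader can recover the right effect size. No hypothesis, analysis or decision rule uses 0.26. This stands, and it limits the point to one sentence. It does not make the sentence correct.

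A second reply is that the planned analysis adjusts for baseline and so is more sensitive than the sample-size calculation. This also stands. A reader might infer that the trial has 44% power at 0.26 whatever the analysis, or that it has no useful power below 0.47. The documents do not support either inference: both figures belong to the unadjusted calculation, and even without adjustment the detectable effect at 80% power is 0.40. But the section expressly leaves baseline adjustment out of its calculation, so adjustment cannot be the source of 0.26, and plausible correlations do not reach it.

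Two further inferences are tempting.

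- The 1.95 points implied by 0.26 lie below the figure in "2.5 points is held as the upper limit of what would be considered a change compatible with equivalence". That sentence goes on to limit itself to trials that compare two interventions, and the section contrasts these with trials against usual care, which is this trial's design. The comparison adds nothing to the arithmetic.
- A null result might be read as excluding effects near 0.26. The article sets no such rule, and a null result would ordinarily be read from the estimate and its confidence interval.

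Finally, the words small to medium can stay. On the usual benchmarks of 0.2 and 0.5, 0.47 still lies between small and medium. Only the number is shown to be wrong.

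**Conclusion.** The point holds in a narrow form. The effect size of 0.26 is wrong as written: the smallest standardised effect in Table 2, and the one adopted, is 0.47, larger by a factor of about 1.8 (0.467/0.26). No standard reading that was tried recovers 0.26.

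The 0.47 uses only the article's own inputs. The 44% power and the 312 per group also rest on the article's unadjusted basis; the range of 47% to 71% rests in addition on assumed baseline correlations of 0.3 to 0.7. A reader might infer that the sample size itself is wrong or that the trial misses its own target. It does not: 97 per group gives 90% power for 3.5 points at SD 7.5. The number would come into question only if 0.26 had been the real design target, and nothing in the article says so.

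**What to change.** Replace the sentence with: *The chosen scenario (3.5 points, SD 7.5) corresponds to a minimum standardised effect size of 0.47 at 90% power, before any gain from baseline adjustment.* It would sit best after the paragraph that selects the scenario, since it describes that cell and not the table as a whole.

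If the authors did derive 0.26 in some other way, they should state the derivation and its assumptions instead.

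The cost is one sentence. Table 2, the 97 and 140 per group, the total of 280 and the planned analysis are unchanged. The stated sensitivity becomes less favourable.

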### Trial data collection

Trial data will be collected from participants at baseline, 1 week prerelease and at 1, 3, 6 and 12 months postrelease. Feasibility and pilot studies highlighted that this population often lead chaotic lives and are difficult to follow up in the community.^41^ To address this challenge, the research team will make multiple and sustained attempts to follow up participants at each time point. Community follow-up interviews will be conducted in a convenient location for the participants and where appropriate in the premises of services (eg, National Probation Service or CRC) with which the participant is engaged. Participants will be provided with high street shopping vouchers compensating them for their time at the 3, 6 and 12 months postrelease interviews, although this does not apply to participants who have returned to prison and are interviewed there.

The pilot trial highlighted that some participants can be temporarily lost, but subsequently re-emerge (possibly engaging with community services or back in prison).^41^ Follow-up data collection points will take place within broad time-windows. The 1-month follow-up will take place between 14 and 60 days postrelease, the 3-month follow-up will take place between 61 and 151 days postrelease, the 6-month follow-up between 152 and 244 days postrelease and the 12-month follow-up between 304 and 483 days postrelease. Where feasible, follow-up interviews will take place as close to 1, 3, 6 and 12 months postrelease time points as possible. Furthermore, if a participant misses a follow-up interview (eg, at 3 months), they will continue to be included in the study until all follow-up time-points have lapsed (eg, 483 days postrelease), after which point those remaining out of contact will be regarded as lost. If the research team is in contact with a participant but setting up a face-to-face interview is challenging (or if they have failed to turn up to an appointment), researchers will attempt to complete the CORE-10iii by telephone. However, even when the CORE-10 has been completed, researchers will endeavour to follow up participants with a face-to-face interview.

The numbers and reasons for drop-outs and losses to follow up will be reported for each arm of the study.

#### Baseline and 1 week prerelease data collection

Baseline data collection will usually continue immediately after the screening interview, although additional sessions can be arranged to meet the needs of individual participants or time constraints within the prison. As outlined in table 1, the following data will be collected at this point:psychological distress using the CORE-OM;subjective rating of need across health and social domains using an adapted version of the CAN-FOR;healthcare, criminal justice and other service utilisation using an adapted version of the CSRI;objective social outcomes (accommodation, education, employment);drug and alcohol use and dependence using the TOP and LDQ;health-related quality of life using the EQ-5D-5L;well-being-related quality of life using the ICECAP-A;IOMI;Standardised Assessment of Personality-Abbreviate Scale;Neurodevelopmental Symptoms Rating Scale;experience of traumatic life events using the Trauma Questionnaire.

The questions from the standardised measures, including the primary outcome measure (CORE-OM), will be read out to participants in a precise and consistent manner, to minimise bias and overcome any literacy problems. Questions from the secondary outcome measures are incorporated into a specially constructed flexible interview, which avoids duplication of subject matter in order to reduce disengagement or irritability. Data will be recorded in the Baseline Case Report Form.

In addition to the baseline data collection, the researcher will complete a contact sheet for each participant. This will include contact numbers and addresses provided by the participant, as well as a list of services that they are likely to be in contact with postrelease. This sheet will be completed in collaboration with the participant, and they will sign the form to consent that the research team can contact them via the relevant services.

The researchers will meet with the participant again within the week prior to their release. The service use table from the adapted CSRI, to collect information on services the participant has seen since the baseline data collection, and the Brief Inspire Questionnaire will be completed to measure the participant’s experience of these services. The researcher will also update contact details for the participant.

Information regarding medication prescribed in the 3 months before prison release, as well as any chronic medical conditions or acute conditions in the previous 12 months, will be collected from the prison healthcare records system. Summary data regarding offence history and number of previous custodial sentences will also be collected from prison records.

#### Follow-up data collection

At all follow-up meetings, the researcher will remind the participant of the information sheet and consent, drawing attention to data confidentiality and instances of disclosure where the researcher would need to breach confidentiality.

At approximately 1 month postrelease, the researcher will contact the participant. This follow-up can be completed by phone, but preferably face to face to support continued engagement. The researcher will read aloud to the participant and record responses to the CORE-OM. These data will be used in analysis, but the main objective of the meeting is sustained engagement and planning further contact.

The 3-month, 6-month and 12-month follow-ups will take place between 61 and 151 days, 152 and 244 days and 304–483 days postrelease, respectively, although researchers will endeavour to complete data collection close to the 3-month (90 days), 6-month (182 days) and 12-month (365 days) points. At each time point, participants will be read the questions from the measures listed in table 1.

### Economic evaluation

The cost-effectiveness of the intervention to increase engagement and access to services and to improve mental health outcomes will be assessed. This will be compared with service access and support as usual, using the economic model developed in the pilot phase, populated with the trial outcomes and resource use data up to 12 months postrelease from prison. It will be conducted from a public sector perspective, initially with the same time horizon as the RCT, and primarily using a cost-consequence approach. Within the cost-consequence approach, the estimated incremental costs will be compared with:The number of people provided with the service/intervention.The incremental differences in the main RCT self-reported health outcomes—CORE scores and EQ-5D-5L and ICECAP-A social preference weights.Incremental differences in the number of ex-prisoners who: have resettled; are in employment; have no proven re-offending; are not homeless.Estimated lifetime gains in quality-adjusted life years (QALYs). Improvements in lifetime gains will be linked with short-term gains seen in the trial and will be associated with social inclusion outcomes such as effective resettlement, increased employment or reduced reoffending rates. Sustained improvements in these will be modelled based on evidence from the literature. We will test the impact of differing the duration of the persistence of any short-term gains on QALYs (and associated costs) if there is no evidence in the literature.The cost of providing the intervention will be based on a combination of process of care data collection and intervention practitioner care records and diaries (bottom-up costing approach) and the total costs of service provision (top-down costing). Both deterministic and probabilistic sensitivity analysis will be conducted to explore uncertainty in the model assumptions and parameters, with exploration of key sources of structural uncertainty where feasible.

The analyses will be conducted according to current guidance from the International Society for Pharmacoeconomics and Outcomes Research on best practice for conducting trial-based economic evaluation.^58^ Consistent with the analytical approach used in the statistical analysis of the effectiveness outcomes of the RCT where possible; the cost-effectiveness analysis will be reported in accordance with the Consolidated Health Economic Evaluation Reporting Standards.^59^

### Process evaluation

The process evaluation will be conducted in parallel with the trial and will adopt a mixed-methods, realist-informed, approach.^60^ During the development and piloting of the Engager intervention we produced and refined a theoretically informed, and evidence-based, logic model of the ways in which the intervention was understood to work,^61^ which we intend to test in the process evaluation. The logic model included the core components of the intervention that the practitioners were asked to deliver, the key mechanisms of impact (ie, how what the practitioners were doing was understood to produce the desired outcomes) and the anticipated outcomes.^62^

### Process evaluation specific objectives

to determine the degree to which the core components of the intervention were delivered and the key mechanisms of the intervention occurred;to evaluate the extent to which the core components and key mechanisms of the intervention produced the intended outcomes;To explore any unintended consequences of delivering the intervention;to identify aspects of the intervention and delivery that could be improved;to identify any aspects of intervention delivery that require additional input from practitioner teams when the research team is no longer in place;to develop an understanding of how to deliver the intervention in real-world settings (training, supervision, meta-supervision).

### Data collection

The data collection methods were developed and refined for acceptability in the pilot trial Formative Process Evaluation and include:intervention components checklist to measure fidelity to the intervention;semistructured interviews, with a purposively selected subsample of participants, some on one occasion and some at regular intervals throughout their participation in the trial;semistructured interviews with Engager practitioners and supervisors throughout the trial;semistructured interviews with other practitioners and team leaders, in other services about their perceptions of, and interactions with, the Engager practitioners, participants and the intervention;semistructured interviews with family/partners/friends of participants receiving the Engager intervention;audio-recordings of practitioner group supervision sessions;audio-recordings of selected practitioner–participant interactions;Engager practitioner records and notes;quantitative outcome measures, contained within the case report form (CRF), and also being used as part of the main trial outcomes;ethnographic field notes recorded by the process evaluation researchers.

### Data analysis

The framework analysis methodology, which we developed and applied in the Formative Process Evaluation, will be used and extended to collate and interrogate the process evaluation data.^63^ The deductive components of the framework will be informed by the logic model’s key mechanisms of impact, that is, the ways in which we understand the intervention to be working. Inductive components of the framework will be surfaces as part of the analytical process. At the end of this analytical process, the logic model of the key mechanisms of impact of the intervention will be revised.

The process evaluation researchers will be distinct from the researchers collecting outcome measures. They will contribute to the qualitative, and therefore more subjective, data collection and the overall analysis. A ‘critical friend’ researcher, external to the outcome measure and delivery teams, will facilitate the process evaluation researchers’ opportunity to self-reflexively explore how their presence affects their data collection and experiences in the field, which may influence their analytical processes.^62^ When the process evaluation data and analysis can contribute to refining ongoing fidelity to the Engager model, it will be fed back directly to the intervention delivery team. When the process evaluation data and analysis concerns the outcomes of interest, the data will be shared after the trial database has been locked down and initial statistical analyses have been carried out.

If the main trial does not demonstrate that the intervention is effective, additional analysis of the qualitative data will be conducted using thematic methods to explore possible explanations for this^64^ and to glean any additional learning that may have application to other studies with socially marginalised populations and/or those with mental health needs.

### Serious adverse events

Non-serious adverse events will not be recorded. Serious adverse events (SAEs) will be recorded and reported. Any SAEs deemed to have a causal relationship to trial participation with be reported to the sponsor within 24 hours of the chief investigator being informed.

### Study timeline

Study start date: 14 January 2016.

Trial registration date: 4 February 2016.^iv^

Projected end date for recruitment: 30 September 2017.

Projected end date for 6-month follow-up data: 31 July 2018.

Projected initial analysis of primary outcome data: 30 November 2018.

Projected final report date: 31 October 2019.

Current status: recruiting.

### Data management and statistical analysis plan

All data will be treated confidentially and stored securely and anonymously. CRFs will be checked and signed at the research sites by a member of the research team before being sent to the PenCTU for double-data entry on to a password-protected database. All forms and data will be tracked using a web-based trial management system. Double-entered data will be compared for discrepancies, and discrepant data will be verified using the original paper data sheets.

All quantitative data analyses will be conducted and reported in accordance with Consolidated Standards of Reporting Trials recommendations. We will closely monitor the process of data collection during the trial providing flow diagrams summarising, by group, the numbers approached, recruited, randomised, followed up/lost to follow-up and outcome completion.

Primary analyses will be conducted on an intention-to-treat basis (ie, according to randomised group) and compare primary and secondary outcomes at 6-month follow-up between randomised groups on those with complete data sets. Outcomes will be compared using linear-regression-based methods, adjusting for baseline outcome scores and stratification variables (eg, investigation centre). Where necessary, outcomes will be transformed to ensure good regression model fit. A secondary analysis will compare primary and secondary outcomes between groups at all follow-up time points using a repeated measures approach. Reasons for missing data (including loss to follow-up and participant drop-out) will be documented and the baseline characteristics of those with and without missing data compared. Using different assumptions for missing data, we will undertake sensitivity analyses using various imputation models, comparing between group results to the completers’ primary analysis. We shall also explore the possibility of conducting secondary per protocol between-group comparisons. If possible, this will be based on a predefined minimum level of intervention receivership and using complier average causal effect analysis methods. The analyst will be blinded to group allocation and the analysis will be undertaken using STATA V.14.2.

A detailed statistical analysis plan will be prepared before any data analysis is conducted. The statistical analysis plan will be agreed with the trial steering committee.

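### The primary 6-month comparison is complete-case and leaves out recorded 1- and 3-month CORE-OM scores, although 30% loss is planned and 37–45% was seen before

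*Protocol article*

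**What the plan says.** The section Data management and statistical analysis plan of the protocol article fixes the primary analysis. It explains its label on the spot: "Primary analyses will be conducted on an intention-to-treat basis (ie, according to randomised group". The analysis will then "compare primary and secondary outcomes at 6-month follow-up between randomised groups on those with complete data sets". The model is given as: "Outcomes will be compared using linear-regression-based methods, adjusting for baseline outcome scores and stratification variables (eg, investigation centre". No score taken between release and 6 months enters it.

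The other time points have a separate place: "A secondary analysis will compare primary and secondary outcomes between groups at all follow-up time points using a repeated measures approach". For missing data, "we will undertake sensitivity analyses using various imputation models, comparing between group results to the completers’ primary analysis". Reasons for loss will be recorded, and the baseline characteristics of men with and without missing data compared. A detailed analysis plan is still to be written and agreed with the steering committee.

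Table 1 (Outcome measures) schedules CORE-OM at baseline and at 1, 3, 6 and 12 months, with CORE-10 as a fallback. Of the 1-month scores, Follow-up data collection says: "These data will be used in analysis, but the main objective of the meeting is sustained engagement and planning further contact".

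Sample size plans for 30% attrition and also reports: "Follow-up rates of 63% and 55% were achieved in feasibility and pilot work". Trial data collection notes that "some participants can be temporarily lost, but subsequently re-emerge (possibly engaging with community services or back in prison".

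**The concern.** A complete-case regression on baseline and centre estimates the effect in all randomised men only if, given arm, centre and baseline score, being seen at 6 months is unrelated to the 6-month score. Several features of the design make that doubtful:

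- Men are found partly through services. The contact sheet lists the services each man is likely to use, and interviews may be held on those premises.
- Lost men may reappear through services or in prison, and both states plausibly relate to distress.
- The intervention works to connect men with services and to arrange continuing care. How easily a man can be traced may therefore be partly a consequence of allocation.

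The 1- and 3-month scores carry information about loss of this kind. A man seen at both visits but missed at 6 months contributes nothing to the primary estimate. What is at stake is bias in the headline result, more than power.

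**Working it through.** **1. The plan's own figure.** Inputs from Sample size: difference 3.5, SD 7.5, 90% power, two-sided 5%. 
n per group = 2(1.960 + 1.282)² × 7.5² / 3.5² = 2 × 10.51 × 56.25 / 12.25 ≈ 96.5, so 97, as stated. All twelve cells of Table 2 reproduce. 97 / 0.70 = 138.6, so 139 against a stated 140; 140 × 0.70 = 98 evaluable.

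**2. How many men leave the primary estimate.** Power is unadjusted, for 3.5 points with SD 7.5.

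| 6-month follow-up | Analysed of 280 | Left out | Power |
|---|---|---|---|
| 70% (planned) | 196 | 84 | 90.4% |
| 63% (earlier work) | about 176 | about 104 | 87.3% |
| 55% (earlier work) | 154 | 126 | 82.5% |

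**3. Bias under assumed dropout.** The documents give no correlations and no dropout model, so these are assumptions, varied over three sets of simulations. All use SD 7.5 and, in this step, assume every 1- and 3-month score is observed.

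- Set A: 2,000 replicates, 280 men, correlation 0.5 or 0.7 between all visits, loss at 6 months depending on the 3-month score. It compares regression on arm and baseline in completers with an estimator that also uses the 1- and 3-month scores.
- Set B: 1,000 replicates, 140 per arm, correlation 0.5 with baseline and 0.65 between follow-ups. Base loss is 25% (intervention) and 37% (control); control dropout odds rise 8–13% per 3-month point, with no dependence in the intervention arm.
- Set C: 1,500 replicates, SD and correlations as in B, log-odds 0.10 per point.

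Effects are shown as point reductions; the true effect is 3.5 in the last two columns.

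| Dropout assumption | Bias, no true effect | Complete-case estimate | Using early scores |
|---|---|---|---|
| Unrelated to score (A) | 0 | 3.51 | 3.51 |
| Same dropout model in both arms (A, C) | about 0.01 | 3.36–3.38 | 3.51 (A) |
| Unequal loss, same dependence (A) | 0.19–0.22 | 3.16–3.22 | 3.51 |
| Controls only, 55% v 70% followed (A) | 0.34–0.71 | 2.79–3.16 | 3.50–3.51 |
| Controls only, as described (B) | 0.59–0.89 | 2.57–2.87 | 3.49–3.50 |

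Set C gives 0.24–0.35 for unequal loss with the same dependence, and 2.74 against 3.52 for the controls-only case. In the controls-only rows of set A, type I error is 7–11% instead of 5%. In the second row the bias with a true effect is 0.12–0.14, because the effect itself makes loss unequal.

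With loss unrelated to score, using the early scores lowers the standard error: in set A from 0.991 to 0.966 (2.5%) or 0.816 to 0.783 (4.0%); in set B from 0.95–0.96 to 0.88–0.90 (5–8%).

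**4. Limits of the remedy (set C, controls-only dependence, true effect 3.5).** If 70% of men lost at 6 months also missed the 1- and 3-month visits, the early-score estimate is 3.02. The bias falls from 3.50 − 2.74 = 0.76 to 3.50 − 3.02 = 0.48, a cut of 0.28 / 0.76 = 37%. If control loss depends on the unseen 6-month score itself, the early-score estimate is 2.55, leaving a bias of 0.95.

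**The case against.** The strongest reply is that the plan is open and already contains the better analysis. The restriction to complete data stands in the same sentence as the intention-to-treat label, which is defined only as analysis by allocated group, and the article itself calls the result a completers' analysis. The early scores are used in the repeated-measures analysis, and imputation under several assumptions is planned. A reader might infer that the label conceals the restriction, or that the early scores are thrown away altogether. Neither is supported.

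A reader might also infer that loss is known to differ by arm and to depend on outcome. It is not: no passage reports follow-up by arm. Every willing intervention participant is offered 8 weeks of contact after release, and the further 12 weeks are for those who need them, at lower intensity. Contact therefore ends by 20 × 7 = day 140, before the 6-month window opens at day 152. Contact sheets cover both arms, nearly all men leaving prison are supervised, and CORE-10 can be taken by telephone. The 37% and 45% losses come from earlier work, and the article gives reasons for expecting 30% or less.

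These points limit the size and certainty of the concern but do not remove it. Links to services are meant to outlast practitioner contact, so its end before day 152 does not close that route. Sensitivity analyses can expose a problem, yet the main conclusion still rests on the completers' estimate. The later analysis plan is not an answer either, since it would have to reverse a stated choice and not merely add detail.

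**Conclusion.** The point holds as a recommendation to change which analysis is primary. The plan rests its main conclusion on a complete-case estimate whose validity needs loss to depend on nothing beyond arm, centre and baseline, while potentially informative scores are confined to secondary work.

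The bias may be negligible, about 6–10% of the 3.5-point target (0.2–0.35), or about 9–26% of it (0.3–0.9), depending on dropout patterns that the documents do not give. The upper range should not be read as the expected size: it needs outcome-dependent loss in controls alone and complete early visits. The direction is also unknown. The simulations assume that high-scoring controls are lost, which shrinks a true benefit; loss of low-scoring controls would push the other way. Power is a lesser issue, staying above 82% at 55% follow-up.

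**What to change.** Before the primary data are analysed, state that the primary analysis is the repeated-measures model already planned, specified as CORE-OM at 1, 3 and 6 months with baseline CORE-OM, centre, arm-by-visit terms and an unstructured covariance, and with the 6-month contrast as the primary estimate. Multiple imputation by arm, using the 1- and 3-month CORE-OM and any CORE-10, would serve as well.

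Keep the complete-case regression as a sensitivity analysis and describe it as complete-case. Name missing-not-at-random analyses among the planned sensitivity analyses, because neither alternative corrects loss that depends on the unseen 6-month score. Return to prison should not be relied on as an auxiliary variable unless it is shown to be available at 6 months for lost men: Table 1 lists police records only at baseline and 12 months.

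The cost is a change of wording in the protocol and analysis plan and slightly more modelling, resting on a missing-at-random assumption. No new data and no change in sample size are needed. The gain shrinks if men lost at 6 months also missed the earlier visits.
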